# Effectiveness of lithium in subjects with treatment-resistant depression and suicide risk: a protocol for a randomised, independent, pragmatic, multicentre, parallel-group, superiority clinical trial

**DOI:** 10.1186/1471-244X-13-212

**Published:** 2013-08-13

**Keywords:** Randomised controlled trial, Lithium, Suicide, Deliberate self harm, Mortality, Depression, Treatment resistant, Antidepressant

## Abstract

**Background:**

Data on therapeutic interventions following deliberate self harm (DSH) in patients with treatment-resistant depression (TRD) are very scant and there is no unanimous consensus on the best pharmacological option for these patients. There is some evidence that lithium treatment might be effective in reducing the risk of completed suicide in adult patients with unipolar affective disorders, however no clear cut results have been found so far. The primary aim of the present study is to assess whether adding lithium to standard therapy is an effective treatment strategy to reduce the risk of suicidal behaviour in long term treatment of people with TRD and previous history of DSH.

**Methods/Design:**

We will carry out a randomised, parallel group, assessor-blinded superiority clinical trial. Adults with a diagnosis of major depression, an episode of DSH in the previous 12 months and inadequate response to at least two antidepressants given sequentially at an adequate dose for an adequate time for the current depressive episode will be allocated to add lithium to current therapy (intervention arm) or not (control arm). Following randomisation, treatment is to be taken daily for 1 year unless some clear reason to stop develops. Suicide completion and acts of DSH during the 12 months of follow-up will constitute the composite primary outcome. To preserve outcome assessor blindness, an independent adjudicating committee, blind to treatment allocation, will anonymously review all outcome events.

**Discussion:**

The results of this study should indicate whether lithium treatment is associated with lower risk of completed suicide and DSH in adult patients with treatment resistant unipolar depression, who recently attempted suicide.

**Trial registration:**

ClinicalTrials.gov identifier: NCT00927550

## Background

International guidelines usually define treatment-resistant depression (TRD) as an episode of major depression which fails to respond to two or more antidepressants given sequentially at an adequate dose and for an adequate time [1-3]. Interestingly, there is no unanimous consensus on the best pharmacological option in these patients: recommendations include switching to a different antidepressant, combining two antidepressants and adding another drug, like lithium, atypical antipsychotics, thyroid hormone, lamotrigine or pindolol [4]. Moreover, an important clinical feature frequently associated to such a difficult to treat population is that in TRD suicidal thoughts are common. They represent alarming psychopathological symptoms,[5] which may lead to deliberate self harm (DSH), suicide attempts and, in up to 10% of cases, to completed suicides [6].

Unfortunately, data on therapeutic interventions following non-fatal suicidal behaviour in patients with TRD are very scant. Hawton and colleagues carried out a Cochrane review to evaluate the effect of specific treatments for patients with depression and history of DSH [7,8]. Only three studies were found and the summary odds ratio (OR) indicated only a non-significant trend towards reduced repetition of DSH for antidepressant therapy compared with placebo (OR 0.83, 95% confidence interval (CI) 0.47 to 1.48). In addition to antidepressants, a possible beneficial effect in terms of suicidal behaviour has been suggested for lithium [9]. In a systematic review and meta-analysis of 32 trials recruiting patients with mood disorders, lithium was more effective than placebo on the risk of suicide, DSH and all-cause mortality, even though these differences were not statistically significant. Some limitations of this systematic review should be borne in mind: the included trials were not primarily designed to measure this outcome and heterogeneous patient populations were enrolled, including unipolar and bipolar patients. Another meta-analysis focused specifically on patients with recurrent, unipolar major depressive disorder and suggested for lithium an antisuicidal effect similar in magnitude to that found in bipolar disorders [10]. However, the major limitation of this analysis is that non-randomised studies were included in the analysis and this may have led to biased results.

In 2008, the results of a randomised, placebo-controlled trial focusing on the suicide preventive effects of lithium in patients with suicidal behaviour were published [11]. In this multi-centre trial (the SUPLI Study), patients with a recent history of a suicide attempt were treated double blind with lithium or placebo and followed up for 12 months. Of 167 patients included in the analysis, only 75% had a diagnosis of major depression: 20% of the whole sample had a diagnosis of adjustment disorder and 5% was suffering from dysthymia or related depressive disorders [12]. Survival analysis showed no significant difference of suicidal acts between lithium and placebo-treated individuals (adjusted hazard ratio 0.52; 95% CI 0.18 to 1.43). However, post hoc analysis revealed that all completed suicides had occurred in the placebo group accounting for a significant difference in incidence rates (p=0.049). Lauterbach and colleagues have suggested that lithium may specifically have suicide preventive effects because in their RCT all of the observed suicides occurred in the placebo group and none in the lithium group. However, the overall number of events was very small (all three suicides in the placebo group) and the lithium-treated individuals were at a higher risk as a result of the significant difference in number of previous suicide attempts which is the most reliable predictor for further suicidal behaviour [13]. Moreover, it also seems that the potential antisuicidal effect of lithium was independent from its mood-stabilising effects. Speculations about possible mechanisms of action involving the central serotonin system have been suggested, because lithium is thought to facilitate 5-HT neurotransmission [14] or may exert its antisuicidal effects influencing aggressive and impulsive traits that are linked to serotonergic dysfunction and also involved in the mediation of suicidal behaviour [15,16]. Evidence from this study suggested lithium treatment to be effective in reducing the risk of completed suicide in adult patients with unipolar affective disorders, however no clear cut results were found in terms of DSH (or suicidality) and the heterogeneity in terms of diagnosis of the recruited sample might have acted as an important confounder.

The primary aim of the present study is to assess whether adding lithium to standard therapy is an effective treatment strategy to reduce the risk of suicidal behaviour in long term treatment of people with TRD and previous history of DSH. Secondary aims of the study are: (a) to assess whether adding lithium has a specific impact in improving depressive symptoms; (b) to assess the long term tolerability profile of the lithium-augmentation strategy.

## Methods/Design

In a multi-centre, 12-month, superiority trial, we will randomise patients with TRD and history of DSH to (i) add lithium to usual treatment (add-on lithium strategy) or (ii) avoid lithium in usual treatment (without-lithium strategy). To be as close as possible to clinical practice, patients and clinicians will not be blind to treatments provided during the trial. However, to limit the potential bias introduced by lack of blindness, an independent adjudicating committee, blind to treatment allocation, will validate the events that will constitute the primary outcome. Patients will be assessed at baseline before randomisation and then every month after random allocation until the completion of the 12-month follow-up. All phases of the trial will be recorded following the CONSORT statement [17,18].

### Study population

Patients will be recruited in Italy. Community psychiatric services agreeing to take part to the study will be asked to recruit consecutive patients meeting the inclusion/exclusion criteria. Patients will be referred either from psychiatric wards or from community-based outpatient clinics. A total number of 50–60 psychiatric services will be involved. During the routine medical consultation relevant patients will be informed of and offered participation in the trial. If the patient agrees to participate in the trial, an appointment will be made for completion of relevant rating scales and questionnaires. Patients will be then randomly allocated to lithium plus usual treatment (either pharmacological or non-pharmacological) or to usual treatment alone.

To take part in the trial all patients must meet all of the inclusion criteria and none of the exclusion criteria, as follows:

#### Inclusion criteria

(a) Diagnosis of major depression (clinical diagnosis, guided by DSM-IV criteria).

(b) An episode of DSH in the previous 12 months.

(c) Inadequate response to at least two antidepressants given sequentially at an adequate dose for an adequate time for the current depressive episode.

(d) Uncertainty about which treatment arm would be best for the participant.

(e) Age 18 or above.

(f) To sign written informed consent.

#### Exclusion criteria

(a) A primary diagnosis of any concurrent Axis I disorder (according to DSM-IV criteria) other than major depression (by contrast, any concurrent DSM-IV Axis II disorder will not constitute an exclusion criterion).

(b) Previous exposure to lithium associated with lack of efficacy or adverse reactions.

(c) Clinical conditions contraindicating lithium (i.e., thyroid or kidney disease/abnormalities).

(d) Pregnant/lactating women and women of childbearing potential not practicing a reliable method of contraception.

### Interventions

Lithium is currently marketed in Italy for the treatment of major depression and it will be prescribed according to Italian usual care. Patients allocated to lithium will be administered an oral starting dose ranging between 150 and 300 milligrams (according to clinical judgement). Suggested final oral dose will have to achieve plasma levels of 0.4 to 1.0 mmol/L. Clinicians will be free of increasing or decreasing the dose according to clinical status and circumstances. Dose changes will be recorded. Following randomisation, treatment is to be taken daily for 1 year unless some clear reason to stop develops. Patients allocated to the lithium arm will receive usual pharmacological and non-pharmacological treatment as clinically indicated. Any other pharmacological treatment will be allowed.

Patients allocated to the control arm will receive usual pharmacological and non-pharmacological treatment as clinically indicated. Patients allocated to the control arm will not be allowed to receive lithium. Any other pharmacological treatment will be allowed.

Routine care outside the trial continues as usual. During the study, participants will be seen as often as clinically indicated with no extra visits required for the trial.

### Baseline and follow up assessments

Before entering the study, patients will be asked to provide informed consent to participate. The following information will be collected at baseline: sociodemographic and clinical characteristics, diagnosis according to the Mini Neuropsychiatry Interview (MINI) [19], laboratory and electrocardiography (ECG) parameters, severity of illness according to the Quick Inventory Depression Scale (QIDS) [20], a self-rated instruments that has been shown to have good psychometric properties [21]. Detailed information will be gathered on previous DSH acts, as well.

Follow-up data will be obtained each month after random allocation using an electronic form, as follows: any death or DSH, lithium oral dose and plasma level (if applicable), concomitant drug treatments, QIDS scores, adverse events and information on laboratory and ECG parameters.

### Random allocation procedure

Patients will be randomly assigned to one of the two treatment groups with an equal probability of assignment to each treatment (allocation ratio 1:1). A centralised randomisation procedure will be employed. The trial biostatistician will prepare the sequence of treatments randomly permuted in blocks of unequal size. The allocation will be stratified by presence or absence of Axis II diagnosis *(patients with unipolar major depression AND personality disorder vs patients with unipolar major depression WITHOUT personality disorder)* because this variable may have an impact on the study outcomes (see Discussion).The randomisation schedule will be generated using nQuery Advisor, release 7.0. Recruiting physicians will contact an administrator at the World Health Organisation Collaborative Centre for Research and Training in Mental Health and Service Evaluation of the University of Verona who will access a computerised system that will provide, after information on the enrolled participant is entered and inclusion criteria are verified, the patient's identification number and the allocated treatment.

### Outcomes

Suicide completion and acts of DSH during the 12 months of follow-up will constitute the composite primary outcome. The term “suicide” is defined as an act with a fatal outcome, deliberately initiated and performed by the person with the knowledge or expectation of its fatal outcome. DSH is defined as intentional self-poisoning or self-injury, irrespective of motivation, as the intention to end life may be absent or present to a variable degree [7,8]. To preserve outcome assessor blindness, an independent adjudicating committee (three clinical psychiatrists, with no links to the study and blind to treatment allocation) will anonymously review all deaths and all hazardous acts reported during the 12 months of follow-up by the treating clinicians. The committee will have the role of identifying, among deaths, the cases of suicide, and among hazardous acts those that constitute acts of DSH. Only the cases of suicide and those of DSH validated by the committee will constitute the primary outcome.

As secondary outcomes, we will consider number of events (acts of DSH), number of suicides and all-cause mortality, change in severity of depressive symptoms from baseline to endpoint and adverse reactions during the 12 months of follow-up.

### Power analysis and sample size calculation

When we first drafted the study protocol, the sample size calculation was based on data from three antidepressant clinical trials that employed completed and attempted suicide as the primary endpoint [7,8] (for details, see clinicaltrials.gov, ClinicalTrials.gov identifier: NCT00927550). However, the most recently published evidence has shown that the event rate of completed and attempted suicide in patients with unipolar, recurrent depression (with or without Axis II diagnosis) is higher than expected and can be more than 35% at 12 months [22,23]. According to this data, hypothesising that lithium augmentation (experimental group) would show a clinically significant advantage by producing an event rate of 10% [7,8], a sample size of 210 patients (105 in each group) achieves 80% power for a 0.05 level of two-sided log-rank test (31 events expected).

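### The sample-size paragraph cannot be right as printed: more than 35% against 10% in 210 patients gives at least 47 events and about 99% power, not 31 events and 80%

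*Protocol article*

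**What the plan says.** All the figures stand in one paragraph of the Protocol article, Power analysis and sample size calculation. It explains that an earlier calculation was replaced because newer evidence shows that the rate of completed and attempted suicide "is higher than expected and can be more than 35% at 12 months". It presents the new calculation as following from that evidence and hypothesises that lithium "would show a clinically significant advantage by producing an event rate of 10" per cent. The result is that "a sample size of 210 patients (105 in each group) achieves 80% power for a 0.05 level of two-sided log-rank test (31 events expected").

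The paragraph gives no other control rate, no hazard ratio, no formula and no allowance for loss. Random allocation procedure sets the allocation at 1:1, and Outcomes fixes follow-up at 12 months. Statistical analysis says that patients lost during follow-up are censored, without giving an expected proportion.

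**The concern.** A reader takes 35% and 10% as the design rates, because they are the only two printed and the calculation is said to follow from them. On those rates the expected control-arm events alone exceed the total stated for the whole trial, which can be seen without any power formula.

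This paragraph defines the effect that the trial is built to detect. As printed, nobody can tell whether 80% power refers to a reduction from 35% to 10% or to something smaller. A null result could then be described as coming from a trial with 80% power for 35% against 10%, which does not follow from the figures. Nor can the 210 be checked.

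**Working it through.** **Inputs.** Control rate 35% (the lower limit of the printed wording), lithium rate 10%, 105 per arm, two-sided alpha 0.05, power 80%, 31 events: all from Power analysis and sample size calculation. Proportional hazards and no losses are assumed unless stated.

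**1. Expected events.** Control 105 × 0.35 = 36.75. Lithium 105 × 0.10 = 10.5. Total 47.25, against the stated 31. A control rate above 35% widens the gap: at 40% the total is 105 × 0.50 = 52.5.

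**2. Implied hazard ratio.** HR = ln(1 − 0.10)/ln(1 − 0.35) = 0.1054/0.4308 = 0.245.

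**3. Power with 47.25 events.**
- Schoenfeld: z = √47.25 × |ln 0.245|/2 − 1.96 = 6.874 × 1.408/2 − 1.96 = 2.88, power 99.8%.
- Freedman: z = √47.25 × (1 − HR)/(1 + HR) − 1.96 = 6.874 × 0.607 − 1.96 = 2.21, power 98.7%.
- Simulated log-rank test, exponential times, 4000 runs: 99.6%.

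**4. What 80% power would need at this hazard ratio.** (1.96 + 0.842)² = 7.85, and the mean event rate is (0.35 + 0.10)/2 = 0.225.
- Schoenfeld: 4 × 7.85/1.408² = 15.8 events, N = 15.8/0.225 = 70.
- Freedman: 7.85 × (1.245/0.755)² = 21.3 events, N = 21.3/0.225 = 95.

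The printed 210 is two to three times this.

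**5. Can losses explain it?** Going from 47.25 to 31 events means losing 1 − 31/47.25 = 34% of events. Even then, 31 events at HR 0.245 give z = 5.568 × 1.408/2 − 1.96 = 1.96 (97.5%, Schoenfeld) or z = 5.568 × 0.607 − 1.96 = 1.42 (92.2%, Freedman). A loss allowance could bring the event count down to 31, but it does not bring power down to 80%. Taking the hazard ratio as the plain ratio of rates, 0.10/0.35 = 0.286, 31 events still give 87% to 94%.

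**6. What could have produced 31 events and 210 patients?** Keep lithium at 10% and let the control rate and the loss vary.
- Control 25%: HR = 0.366. Schoenfeld needs 31.1 events and N = 31.1/0.175 = 178. With 15% loss, 178/0.85 = 209.4, that is 210.
- Control 25%, Freedman, no loss: 36.5 events and N = 208. This fits the 210 but not the 31.
- Control 27.2%: HR = 0.332. Freedman needs 31.2 events and N = 31.2/0.186 = 168. With 20% loss, 168/0.80 = 210.

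More than one pair fits, and none of these control rates or losses is printed.

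**7. Effect detectable with 80% power at 31 events.**
- Schoenfeld: HR = exp(−2 × 2.802/√31) = 0.37.
- Freedman: (1 + HR)/(1 − HR) = √31/2.802 = 1.987, so HR = 0.987/2.987 = 0.33.

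**The case against.** The best defence is that the paragraph never labels 35% as the design rate. It says that the rate can exceed 35%, which describes the upper end of the cited evidence. The investigators may have designed on a lower rate that was lost when the article was condensed. This has force: it makes an unprinted control rate more likely than a slip in the calculation. It does not remove the problem, because the calculation is presented as resting on that evidence and no other control rate appears anywhere in the article. The figures are also not merely abbreviated. Two rates, a sample size, a power and an event count are all printed, and they disagree.

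A second defence is that conduct and analysis are unaffected. That stands. If the true control rate is near 25%, simulated power with 210 patients is about 82% without losses and 79% with 15% loss. At 35% it is about 99%.

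Three stronger readings are tempting but not supported:
- *The control rate must have been 25%.* It is one candidate. It yields both 31 events and 210 patients only by Schoenfeld with about 15% loss, which is not stated, and 27.2% with 20% loss by Freedman fits equally well.
- *True power is only about 50%.* Taking 31 events literally, with 10.5 on lithium, leaves 20.5/105 = 19.5% in control, HR 0.485 and power of 49% to 52%. This assumes no losses and that 31 is the number expected in 210 patients. If 31 is the number required by a formula, the figure does not arise.
- *The trial is underpowered against the earlier lithium trial.* Background reports an "adjusted hazard ratio 0.52; 95% CI 0.18 to 1.43" for that trial. The interval contains both 0.245 and 0.37, and the sample was diagnostically mixed, so it does not contradict the design effect. Whether 10% on lithium is optimistic is a separate matter of judgement.

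**Conclusion.** The point holds. Taken together, a control rate of at least 35%, a lithium rate of 10%, 210 patients, 80% power and 31 events are inconsistent. On the printed rates the trial would expect at least 47 events rather than 31 and would have about 99% power rather than 80%. The event count needs only multiplication. The power rests on proportional hazards and no losses, but every variant tried at 35% against 10% stayed well above 80%, including one with events cut to 31.

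The 80% and the 31 therefore depend on a control rate, and possibly a loss allowance, that the article does not give. The document does not allow that rate to be identified. Nor does it show that 210 patients are too few. The stated basis is what is wrong, and it should be corrected because the trial's power claim for its primary outcome depends on it.

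**What to change.** Restate the paragraph from one consistent set of inputs: the control rate, the hazard ratio, the formula or software routine and the loss allowance actually used, with sample size, events and power that follow from them.

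- If 35% is the design rate, state about 47 expected events and about 99% power without losses.
- If a lower rate was used, print it in place of 35% as the design rate and say why it was chosen. Say also whether 31 is the number of events required by the formula or the number expected in 210 patients.
- In either case add the hazard ratio detectable with 80% power at 31 events: 0.33 (Freedman) to 0.37 (Schoenfeld).

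The cost is one corrected paragraph. The stated assumption may become less favourable, or the stated power may change. No change in the number of patients is needed.

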### Statistical analysis

The statistical analysis will be masked, i.e. the trial biostatistician will be blinded to the treatment groups until the analysis has been completed. All analyses will be performed using Stata/SE, Release 11.1. Data lock will occur at 12 months, when data will be available for all participants. The pattern of missing values will be explored and interactions between treatment group and non-completers/completers will be examined with respect to demographic variables and baseline disease assessment.

The intention-to-treat (ITT) population, consisting of all subject randomly assigned to the competitive treatment strategies, will be used for the analysis of primary and secondary outcomes. Patients with missing values and patients lost during follow-up will contribute to the analysis of the primary and secondary outcomes only for the time during which data are available (censoring). Missing values in depressive symptom ratings will be imputed using the last observation carried forward (LOCF) approach: depressive ratings will be carried forward from the last available assessment to the 12-month follow up assessment. Additionally, patients in each arm will be always analysed according to the corresponding treatment group’s allocation at baseline.

In order to check the consistency of this ITT approach, the primary outcome will then be analysed using a per-protocol (PP) approach. The analysis of the PP population will be used for confirmatory purposes only. If less than 5% of patients switch from the allocated treatment to the competitive treatment, the PP analysis will not be performed.

Kaplan-Meier estimates for the time from randomised treatment assignment until the first event that constitutes the primary outcome will be plotted to compare the treatment’s effect, and log-rank test will be performed to test for differences. A Cox proportional hazard model will be used to explore the effect of possible confounding or interaction factors. Gender and age will be included into the model regardless of statistical significance criteria. The proportional hazard assumption of the effects will be tested. No interim analysis is planned for this trial.

Time from randomised treatment assignment until all-cause mortality during the 12 months of follow-up will be analysed through a log-rank test for difference in survival between the two groups. The same method will be applied for the following secondary outcomes: suicide mortality, deliberate self-harm. Multivariate analyses will be performed to explore the possible role of prognostic factors on outcomes.

Change in severity of depressive symptoms from baseline to 12 months will be analysed as a continuous variable and as a dichotomous variables, where individuals showing an improvement of al least 50% will be considered treatment responders. Change in severity of illness at 12-months will be compared between the two groups of treatment through appropriate statistical methods for repeated measurements (paired t-test or McNemar non parametric test according to the variables distribution). The number of events/outcomes of interest (suicide or DSH) will be compared between the two groups of treatment through the chi-square test (or the Fisher’s exact test when appropriate). When possible, a multivariate analysis will be performed through a Poisson regression model with a robust error variance.

The proportion of patients with adverse reactions during the study will be compared between the two groups of treatment through the chi-square test (or the Fisher’s exact test when appropriate).

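### LOCF to month 12 is the only stated method for missing depression ratings and can create a spurious arm difference in a secondary outcome, although QIDS is collected monthly

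*Protocol article*

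**What the plan says.** All quotes are from the protocol article.

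- **Statistical analysis**, on missing scores: "Missing values in depressive symptom ratings will be imputed using the last observation carried forward (LOCF) approach". The sentence goes on to fix the target: "depressive ratings will be carried forward from the last available assessment to the 12-month follow up assessment".
- **Statistical analysis**, the sentence just before: "Patients with missing values and patients lost during follow-up will contribute to the analysis of the primary and secondary outcomes only for the time" in which they have data. The protocol labels this rule censoring.
- **Statistical analysis**, on use of the scores: "Change in severity of depressive symptoms from baseline to 12 months will be analysed as a continuous variable", and also as a yes/no response defined by at least 50% improvement.
- **Outcomes**: the secondary outcomes include "change in severity of depressive symptoms from baseline to endpoint and adverse reactions during the 12 months of follow-up".
- **Baseline and follow up assessments**: "Follow-up data will be obtained each month after random allocation using an electronic form". The items listed include "concomitant drug treatments, QIDS scores, adverse events and information on laboratory and ECG parameters".

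The article also plans to explore the pattern of missing values and to compare completers with non-completers by arm. That comparison uses demographic variables and baseline disease measures. The article attaches no change in the depression analysis to what it finds.

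**The concern.** LOCF takes the last rating, however early, and treats it as the month-12 rating. A patient with only a baseline score enters with a change of exactly zero. Patients join during a current episode that has resisted treatment and are then treated for a year, so a score that stays fixed after the last contact is hard to defend.

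For the arm comparison, the difficulty arises when one arm loses more data, or loses it earlier, while scores are moving. LOCF then gives that arm less of the average improvement, and the shortfall looks like a treatment difference. The quantity at stake is the answer to secondary aim (a), whether adding lithium improves depressive symptoms, both as a mean change and as a response rate.

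Death is a second difficulty. The LOCF sentence makes no exception for it. Read literally, a patient whose score had halved and who then died would be carried forward as a responder at 12 months, in a trial whose primary outcome includes suicide.

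The monthly scores that would permit a better analysis are already collected. A month-12 LOCF analysis uses one post-baseline score per patient, so up to 11 of the 12 monthly values play no part.

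**Working it through.** The plan states no figure on this point, so there is nothing to reproduce. The documents give no QIDS drop-out, mean change or standard deviation; all of these are assumptions below.

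**Inputs**
- From the article: monthly QIDS for 12 months; LOCF to month 12; 105 patients per arm.
- Assumed: no true arm difference; linear mean improvement of D points over 12 months in both arms, D = 4, 6 or 8; drop-out proportions p(L) on lithium and p(C) on control; last rating equally likely at each of months 0 to 11.

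**Formula.** A patient last seen at month k is credited with D × k/12, a shortfall of D × (12 − k)/12. The mean share of follow-up lost is

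(12 + 11 + … + 1)/(12 × 12) = 78/144 = 0.542.

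Spurious difference = [p(L) − p(C)] × D × 0.542, where a positive value makes lithium look worse.

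| Drop-out, lithium vs control | D = 4 | D = 6 | D = 8 |
|---|---|---|---|
| 20% vs 20% | 0 | 0 | 0 |
| 30% vs 20% | 0.22 | 0.33 | 0.43 |
| 30% vs 10%, or 40% vs 20% | 0.43 | 0.65 | 0.87 |
| 20% vs 30% | −0.22 | −0.33 | −0.43 |

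Relative to the assumed improvement, this is 0.10 × 0.542 = 5% to 0.20 × 0.542 = 11%.

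**Earlier drop-out.** If last ratings fall evenly over months 1 to 6, the mean last month is 3.5. With D = 6 the credited improvement is 3.5 × 0.5 = 1.75 and the shortfall 4.25. For 30% vs 15%, the spurious difference is 4.25 × 0.15 = 0.64.

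**Timing alone.** With 20% drop-out in both arms and D = 6, but one arm losing patients over months 1 to 6 (share lost 8.5/12) and the other over months 0 to 11 (share lost 6.5/12), the difference is 0.20 × 6 × 2/12 = 0.20. Equal percentages do not remove the bias if timing differs.

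**Simulation check.** Assumed SDs were 3 between patients, 0.25 per month for slopes and 2.5 for residual error, with 4,000 patients per arm and D = 6. Drop-out was independent of the scores. The comparator was a linear mixed model with random intercept and slope on the observed monthly scores.

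| Drop-out | LOCF difference | Mixed-model difference |
|---|---|---|
| 30% vs 10% | 0.57 | −0.10 |
| 40% vs 20% | 0.50 | −0.05 |
| 20% vs 20% | 0.09 | 0.07 |

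For completers the variance of change is 2 × 2.5² + (12 × 0.25)² = 21.5, SD 4.64, so the LOCF difference has a standard error near 4.64 × √(2/4000) = 0.10. The LOCF values agree with the formula (0.65, 0.65 and 0) to within about one and a half standard errors. The mixed-model values are close to zero.

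**False-positive rate.** With 105 per arm, D = 6 and 1,000 simulated trials, a two-sample t-test on LOCF change (chosen here for illustration) rejected at the 5% level in 15.7% of trials for 30% vs 10%, 16.8% for 40% vs 20%, and 5.1% for 20% vs 20%.

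**The case against.** Several points on the other side stand.

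- **No drop-out figures are given.** A reader might infer that data loss must differ because only one arm adds a drug. The article does not support that. Patients are analysed as allocated, follow-up runs alongside routine care, and nothing says that a patient who stops lithium stops giving QIDS scores. Unequal loss is plausible in an open-label add-on trial with a self-rated scale, but the size above is conditional on it.
- **The direction may be harmless to the claim.** If lithium loses more patients and scores are improving, the bias runs against lithium, which is conservative in a superiority trial. A spurious benefit needs control to lose more. The direction cannot be known in advance, and a bias against lithium still gives a wrong answer to the secondary aim.
- **A contradiction between the two missing-data sentences.** A reader might infer one, since the first covers secondary outcomes without exception and depression change is one of them. The natural reading is milder: censoring is a time-to-event rule, and the next sentence gives the specific rule for ratings. What stands is loose wording.
- **Understated standard errors.** This is a common charge against single imputation, but nothing here demonstrates it. Rejection stayed at about 5% with equal drop-out, and the excess with unequal drop-out came with a shifted mean.
- **The article is condensed.** Sensitivity analyses and the handling of deaths may be set out elsewhere, so their absence is not the complaint. The complaint is the method that the article does fix.

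**Conclusion.** The point holds as an improvement to the analysis of one secondary outcome. The primary comparison, a log-rank test on adjudicated suicide and self-harm, is not affected.

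LOCF is a weak main method when up to 12 monthly ratings are available. Under no true effect it is unbiased for the arm comparison if the amount and timing of missing data and the score trends match between arms, so it would be too strong to say that it always biases the result. If they do not match, the spurious difference is about 0.2 to 0.9 QIDS points for a drop-out difference of 10 to 20 percentage points, given linear improvement of 4 to 8 points and last ratings spread over months 0 to 11. Its sign follows whichever arm loses more. The documents state no threshold for an important QIDS difference, so this size cannot be judged against one. At the planned 105 per arm it could roughly triple a nominal 5% error rate in the 20-point scenarios, under the assumed SDs.

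The responder problem after death follows from the rule as written; whether it would occur in practice depends on handling that the article does not describe.

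**What to change.** 1. Make the main analysis a mixed model for repeated measures on all observed monthly QIDS scores, with arm, month, arm by month, baseline QIDS and Axis II stratum. Report the month-12 arm contrast as the estimate.
2. Derive 50% response at 12 months by multiple imputation from the same model, with patients who died counted as non-responders.
3. State that the continuous month-12 contrast is hypothetical with respect to death. The mixed model also projects scores past death, so this should be declared.
4. Keep LOCF, if at all, as a sensitivity analysis.
5. Reword the censoring sentence so that it applies to the time-to-event outcomes only.

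No new data or visits are needed. The cost is revised analysis wording and slightly more programming. The downside is reliance on a missing-at-random assumption, which the observed data cannot verify. The simulation above, with drop-out unrelated to the scores, does not test it.
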